### Interim analyses {21b}

No interim analysis is planned.

### Methods for additional analyses (e.g., subgroup analyses) {20b}

Exploratory analysis regarding the primary outcome will be performed by comparing both arms of the study in the following subgroups of patients: age greater or lower than its median value, SAPS2 greater or lower than its median value, SOFA score at randomization greater or lower than its median value, renal SOFA at randomization < 2 and ≥ 2, bicarbonates at randomization < 22 and ≥ 22 mmol L^−1^, driving pressure at randomization greater or lower than its median value, plateau pressure at randomization greater or lower than its median value, compliance of the respiratory system at randomization greater or lower than its median value, mechanical power at randomization greater or lower than its median value, PaO_2_ at randomization ≤ 100 mmHg and > 100 mmHg, and pH at randomization greater or lower than its median value.

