### Sample size {14}

The sample size was computed through data simulations based on the following hypotheses:
Ninety-day mortality 45% in the control group, and 40% in the intervention group (i.e., relative reduction 11%)Mean ± standard deviation (*SD*) VFD at day 60 28 ± 16.5 in the control group and 34.5 ± 13 in the intervention group

The expected mortality in patients with COVID-19 and moderate to severe ARDS is between 34 and 50% [1]. The mean and *SD* of VFD at day 60 in the control group was taken from the subgroup of patients with PaO_2_/FiO_2_ < 150 mmHg included in the control group of the prospective randomized Xtravent-study comparing ultra-protective ventilation with extracorporeal CO_2_ removal versus conventional protective ventilation [7]. To be conservative, we have chosen to take an expected difference between the two groups of the present study corresponding to 50% of the difference observed in the Xtravent-study between the control and the intervention groups.

For each scenario corresponding to a given sample size, 1000 datasets were simulated. For each simulation, the score was computed for each patient and compared between the two groups using the test of Mann and Whitney. The power was computed as the proportion of tests with a bilateral *p*-value < 0.05.

The results of the simulations allowed us to determine that the inclusion of 100 patients per group will achieve a power greater than 80% to conclude a significant difference between the groups.

The simulations were implemented by two biostatisticians with the SAS software, version 9.4 (Copyright (c) 2002–2003 by SAS Institute Inc., Cary, NC, USA) and the R software, version 3.6.1 (R Core Team (2012)). The results were similar.

To account for premature exits from the study (withdrawal of informed consent for example), we have planned to add 10% more patients (10 supplementary patients in each group for a total of 220 patients).

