#### Analysis of the secondary outcomes

The analysis of the secondary objectives will also be carried out by intention to treat. Qualitative secondary outcomes such as the mortality at day 90 will be described in each group by the event proportion and compared using the *χ*^2^ test or the exact test of Fisher. Quantitative secondary outcomes such the VFD at day 60 will be described in each group by the mean and the standard deviation or the quartiles, and the minimum and maximum values according to the shape of the distribution. They will be compared between the two groups using the *t* test of Student or the test of Mann and Whitney.

All the analyses will be carried out using the SAS software, version 9.4 (Copyright (c) 2002–2003 by SAS Institute Inc., Cary, NC, USA). The comparisons will be considered statistically significant for a bilateral *p*-value < 0.5.

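### The exploratory subgroup analyses compare the arms inside each level of 11 two-level variables and name no test of whether the ULTV effect differs between levels

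*Protocol article*

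**What the plan says.** The protocol article, under Methods for additional analyses {20b}, opens with "Exploratory analysis regarding the primary outcome" and says it "will be performed by comparing both arms of the study in the following subgroups of patients". The list begins "age greater or lower than its median value, SAPS2 greater or lower than its median value" and has 11 variables:

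- Eight are split at the median: age, SAPS2, SOFA, driving pressure, plateau pressure, compliance, mechanical power and pH.
- Three have fixed cut-offs: renal SOFA at 2, bicarbonates at 22 mmol/L and PaO2 at 100 mmHg.

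That makes 22 between-arm comparisons. The article names no interaction test, no estimate of the difference between subgroups and no statement on multiplicity, here or elsewhere. At the end of the section on secondary outcomes, a sentence about comparisons in general attaches a significance threshold: "The comparisons will be considered statistically significant for a bilateral *p*-value < 0.5". The sample size section uses 0.05: "The power was computed as the proportion of tests with a bilateral *p*-value < 0.05". The two thresholds must be reconciled. That is a separate matter, and 0.05 is used below.

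**The concern.** A subgroup analysis asks whether the treatment effect depends on a patient characteristic. A p-value in each half answers something else: whether there is evidence of an effect in that half alone. With half the patients, each comparison has low power, so one half will often reach significance and the other miss it even when the effect is identical in both. Such a split is easily read as showing who benefits, for example patients with high driving pressure or low compliance. Readers are likely to take up that kind of statement from a ventilation trial, whether or not it is labelled exploratory.

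**Working it through.** **Inputs** (Sample size {14}): "Ninety-day mortality 45% in the control group, and 40% in the intervention group"; "VFD at day 60 28 ± 16.5 in the control group and 34.5 ± 13 in the intervention group"; 100 patients per group; two-sided 0.05. The plan's test: "the score was computed for each patient and compared between the two groups using the test of Mann and Whitney".

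**Assumptions not in the article:** ventilator-free days (VFD) among survivors are normal with the stated means and SDs (raw, or rounded and clipped to 0–60); deaths rank lowest and are tied; subgroup variables are independent of each other and of outcome; each half has about 50 patients per arm.

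**1. The plan's own figure.** In simulation (2,000 datasets per scenario), scoring each patient against the other arm and applying Mann-Whitney to those scores gives power 0.81 at 100 per group. This matches the stated figure of more than 80%. With identical arms, however, the same procedure rejects in about 88% of trials, because tied deaths receive different scores in the two arms. That is a separate issue. The subgroup check therefore uses a rank test on the ordered outcome, which rejects in about 5–6% of trials with identical arms. Its power at 100 per group is 0.36–0.37.

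**2. Power in one half.** Overall power of 0.37 corresponds to an expected z of 1.96 − 0.33 = 1.63. In a half it is 1.63/√2 = 1.15, so power ≈ Φ(1.15 − 1.96) = Φ(−0.81) ≈ 0.21. Direct simulation at 50 per arm gives 0.21.

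**3. Exactly one half significant, same effect in both.** The two halves contain different patients, so the probability is 2p(1 − p) = 2 × 0.21 × 0.79 = 0.33 per variable. Simulating 11 median splits of the same 200 patients (600 datasets) gives 0.34 per variable and 0.775 for at least one of 11.

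**4. Interaction test on the same data** (difference between the two subgroups' net win proportions over its standard error): 0.056 per variable and 0.47 for at least one of 11. Per variable, the false impression of a differing effect is about six times rarer (0.34/0.056 ≈ 6).

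**5. If overall power really were 80%** (normal model): expected z = 1.96 + 0.84 = 2.80; in a half 2.80/√2 = 1.98; power Φ(0.02) ≈ 0.51; split probability 2 × 0.51 × 0.49 = 0.50 per variable. Simulation gives 0.91 for at least one split among 11, against 0.44 for at least one significant interaction.

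**6. No effect anywhere.** The split probability per variable is 2 × 0.05 × 0.95 = 0.095. Over 11 variables:

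| Model, variables independent | Any subgroup p < 0.05 | Any split verdict | Any interaction |
|---|---|---|---|
| Composite outcome | 0.41 | 0.40 | 0.42 |
| Normal outcome | 0.45 | 0.44 | 0.43 |

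Eleven independent interaction tests give 1 − 0.95^11 = 0.43. The two methods do not separate here.

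**7. Correlated variables.** With a correlation of 0.6 among variables (normal model, 80% overall power), the split verdict stays at 0.51 per variable and 0.90 for at least one of 11; at least one significant interaction falls to 0.34.

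**The case against.** The strongest reply is that the article fixes little. It names no subgroup test, does not say that a split verdict will be read as effect modification, and does not exclude an interaction test. The full protocol and any analysis plan are not shown and may contain one. Comparing arms within subgroups is also how subgroup estimates are obtained, and those are worth reporting. The work is labelled exploratory, and the trial's conclusion rests on the primary analysis.

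Much of this stands. A reader might infer that the plan rejects interaction testing or would base a firm claim on one subgroup; the text supports neither. What remains is that the only method stated is a comparison of arms inside subgroups, in a document that also attaches a significance threshold to comparisons. The exploratory label limits the strength of any claim but does not make this the right contrast.

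Two stronger readings also fail:

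- A reader might treat the 22 comparisons as independent and obtain 1 − 0.95^22 = 0.68 for at least one false positive. The same patients are re-split 11 times, so the comparisons are not independent, and simulation gives about 40 to 47%.
- A reader might infer that interaction tests would remove chance findings. With no true effect, the any-of-11 rate is about the same for both methods. The advantage appears when a real, uniform effect exists.

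**Conclusion.** The point holds as a matter of analysis choice in an exploratory section. It should be corrected but does not touch the primary conclusion. Under a uniform effect of the planned size, within-subgroup testing would suggest a difference that does not exist for about one third of variables, and for at least one of 11 in about 77% of trials. An interaction test does so for about 5% of variables.

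These figures rest on normal VFD among survivors, independent variables, equal halves and a valid rank test at 0.05. The three fixed cut-offs need not give equal halves, and several variables are related. The split rate is higher, about 50% per variable, if the overall test truly had 80% power. If the subgroups used the score-then-Mann-Whitney procedure literally, the figures would not apply: with identical arms that procedure rejected in about 72–74% of simulated trials at 50 per arm.

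**What to change.** Reword the subgroup paragraph under {20b} so that:

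- for each of the 11 variables, the win probability with its 95% confidence interval is reported in each subgroup, together with an estimate and test of the difference between subgroups (the interaction);
- no claim of a differing effect rests on within-subgroup p-values;
- the 11 interaction tests are stated to be exploratory and not adjusted for multiplicity, with about a 43% chance of at least one false positive if they are independent.

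The model can be left to the trial statistician: proportional odds, a probabilistic index model and a direct contrast of win probabilities would all serve. So can any analysis of the modifiers on their continuous scale. The cost is a few sentences and modest programming, with no new data.

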### Methods in analysis to handle protocol non-adherence and any statistical methods to handle missing data {20c}

A per-protocol secondary analysis will be carried out. For this analysis, the patients with major deviations to the protocol will be excluded. In particular, the population of the ULTV arm will be restricted to patients:
With VT ≤ 4.2 mL kg^−1^ (i.e., 4 + 5% to account for measurement error) at least 50% of the days between inclusion and weaning of deep sedation or day 14 whichever comes first, in the intervention groupWith 5.4 ≤ VT ≤ 6.6 mL kg^−1^ at least 50% of the days between inclusion and weaning of deep sedation or day 14 whichever comes first, in the control group

Weaning of deep sedation will be defined as the time at which RASS score is greater than − 3 for at least 48 h or sedation drugs are weaned for at least 48 h.

The frequency of missing data will be described in each group and for each described variable. No method of imputation will be used to replace missing data.

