Within the first hour after randomization, the intervention group will be managed with ultra-low tidal volume ventilation (i.e., aiming for VT 4 mL kg^−1^ PBW, PEEP set using the same PEEP-FiO_2_ table [10], aiming for a plateau pressure < 30 cmH_2_O) under deep sedation (i.e., RASS score between − 3 and − 4 [13]). RR will be set targeting a pH range between 7.20 and 7.45, and VT may be increased if pH remains below 7.15 despite a RR set to 35 min^−1^ and minimization of instrumental dead space (Table 1). This ventilatory protocol was successfully tested in a pilot randomized multicenter trial on 34 patients [8].

Adjustment of ventilatory settings in both groups will be predefined (Table 1). Both ventilatory strategies will be applied until the success of a deep sedation weaning trial (i.e., PEEP decrease down to 5 cmH_2_O with PaO_2_/FiO_2_ ≥ 150 mmHg in the supine position and VT 6 mL kg^−1^ PBW) performed daily from day 3 of the study. In case of ventilator asynchrony or RR > 35.min^−1^ despite ventilatory settings adjustments (Table 1), deep sedation will be resumed and ventilatory strategies will be reapplied according to the allocation group.

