#### Relevant concomitant care permitted or prohibited during the trial {11d}

Patients in both groups will receive deep sedation (i.e., targeting RASS score between − 3 and − 4) after randomization. After a successful deep sedation weaning trial, patients in both groups will be ventilated with VT 6–8 mL kg^−1^ PBW, sedation dose adjusted to target a RASS score between − 2 and 0, and tested daily with a spontaneous breathing test until successful extubation. All ventilatory co-interventions will be standardized to ensure group comparability:
Neuromuscular blocking agent use will be advocated during the first 48 h of ARDS, in case of persisting severe hypoxemia (PaO_2_/FiO_2_ < 100 mmHg with a PEEP > 10 cmH_2_O) or in case of ventilator asynchrony despite deep sedation in assist volume-controlled mode (Table 1).Prone position will be advocated as long as PaO_2_/FiO_2_ < 150 mmHg or PEEP > 10 cmH_2_O or FiO_2_ > 60% in the supine position.Extracorporeal membrane oxygenation (ECMO) will be considered if PaO_2_/FiO_2_ < 60 mmHg in the prone position.ECCOR will be considered in patients with persisting severe respiratory acidosis despite adjustments of the ventilatory settings and pharmacological interventions as defined in Table 1.Recruitment maneuvers will not be recommended.

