#### Secondary outcomes

Ninety-day all-cause mortality.VFD at day 60 after inclusion.Time from inclusion to successful extubation.Successful extubation will be defined as extubation without reintubation or death within 48 h in intubated patients and as weaning of invasive mechanical ventilation for at least 48 h in tracheotomized patients.Length of hospital stay from inclusion.Value of respiratory parameters (PaO_2_/FiO_2_ ratio, pH, PaCO_2_, PEEP, VT, total PEEP, plateau pressure, driving pressure, respiratory rate, MP) assessed daily from inclusion to weaning of deep sedation or 14 days after inclusion whichever comes first.Total PEEP and plateau pressure will be measured at the end of 3-s end-expiratory and end-inspiratory pauses, respectively. Driving pressure will be defined as the difference between plateau pressure and total PEEP. MP will be computed as previously described [14], and partitioned into 3 components:
$$ VT-\mathrm{related}\ \mathrm{MP}=0.0098\times RR\times {VT}^2\times \frac{1}{2}{El}_{rs} $$
$$ \mathrm{PEEP}-\mathrm{related}\ \mathrm{MP}=0.0098\  RR\times VT\times {\mathrm{PEEP}}_{\mathrm{tot}} $$
$$ \mathrm{Resistive}\ \mathrm{MP}=0.0098\times {RR}^2\times {VT}^2\times \frac{\left(1+I:E\right)}{60\times I:E}{R}_{\mathrm{aw}} $$

with RR = respiratory rate, *El*_*rs*_ = elastance of the respiratory system = driving pressure/VT, *I:E* = inspiratory-to-expiratory ratio, *R*_aw_ = airway resistance = (peak airway pressure − plateau pressure)/inspiratory flow.

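### The per-protocol adherence window, and by its wording the daily respiratory outcomes window, can extend past the end of the allocated tidal volume, so protocol-mandated days at 6–8 mL/kg count as non-adherence, mainly in the ULTV arm

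*Protocol article*

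**What the plan says.** All references are to the Protocol article.

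- **When the allocated VT ends.** Intervention description {11a}: "Both ventilatory strategies will be applied until the success of a deep sedation weaning trial". The trial is ventilatory (PEEP lowered to 5 cmH2O, PaO2/FiO2 at least 150 mmHg, VT 6 mL/kg) and is "performed daily from day 3 of the study".
- **What follows.** Concomitant care {11d}: after success, "patients in both groups will be ventilated with VT 6–8 mL kg^−1^ PBW", and the sedation target moves from RASS −3 to −4 up to −2 to 0.
- **If weaning fails.** {11a}: "deep sedation will be resumed and ventilatory strategies will be reapplied according to the allocation group".
- **Analysis window for adherence.** {20c} requires VT ≤ 4.2 mL/kg (ULTV) or 5.4–6.6 mL/kg (control) on at least half of the days from inclusion to weaning of deep sedation, or to day 14 if earlier. The definition of that term begins "Weaning of deep sedation will be defined as the time at which RASS score is greater than" and sets the level at −3, held for 48 h or longer; the alternative is that sedatives have been off for the same length of time.
- **Window for daily VT, plateau pressure, driving pressure and mechanical power.** Secondary outcomes: "assessed daily from inclusion to weaning of deep sedation or 14 days after inclusion whichever comes first". The term is not defined again there. Applying the {20c} definition is an inference from the identical wording.

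**The concern.** Treatment and analysis use nearly the same name for two different events. The weaning trial tests gas exchange at a low PEEP; the {20c} event is a sedation state sustained for 48 h. Deep sedation is the target until the trial succeeds, so in a patient managed to protocol the {20c} event cannot come before the end of the allocated VT and will normally follow it. Nothing in the article removes the days in between.

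On those days a ULTV patient is at 6–8 mL/kg because the protocol says so, yet the day is scored as a failure of the ULTV rule. Two outputs are affected: who enters the per-protocol set, and how much VT separation the trial reports having delivered. Both matter for reading a null result. The burden falls most on patients with few days on allocated VT, that is, those who improve early, so per-protocol membership comes to depend partly on the course after randomization.

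**Working it through.** **Inputs from the article.** Target VT is 4 and 6 mL/kg, so the nominal contrast is 6 − 4 = 2.0 mL/kg. The ULTV limit is 4 × 1.05 = 4.2 mL/kg, which agrees with {20c} ("i.e., 4 + 5% to account for measurement error"). The control band is 5.4–6.6 mL/kg, the threshold is 50% of days, the window is capped at day 14, and the first weaning trial is on day 3. The article states no figure for VT separation over the window or for per-protocol retention, so there is none to reproduce.

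**Assumption.** The lag L, in days from trial success to the end of the window, is not in the documents. It depends partly on whether the 48 h in {20c} closes the window at its onset (L is the time sedation takes to lighten) or at its completion (about 2 days are added). The range shown is L = 0, 1 and 2.

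**Formulas.** Let d be the days on allocated VT and w = min(14, d + L).

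- Share of days at ≤ 4.2 for a fully adherent ULTV patient: d / w.
- Mean contrast over the window, with both arms at the same VT after the trial: 2.0 × d / w.
- Share of the d allocated days that must be at ≤ 4.2 to stay per protocol: 0.5 × w / d.

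With L = 0, these are 100%, 2.0 mL/kg and 50% for every d.

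| d | L = 1: share; contrast; needed | L = 2: share; contrast; needed |
|---|---|---|
| 2 | 67%; 1.33; 75% | 50%; 1.00; 100% |
| 3 | 75%; 1.50; 67% | 60%; 1.20; 83% |
| 5 | 83%; 1.67; 60% | 71%; 1.43; 70% |
| 7 | 88%; 1.75; 57% | 78%; 1.56; 64% |
| 10 | 91%; 1.82; 55% | 83%; 1.67; 60% |
| 12 | 92%; 1.85; 54% | 86%; 1.71; 58% |

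Worked line for d = 3, L = 2: w = 5; 3/5 = 60%; 2.0 × 3/5 = 1.20; 0.5 × 5/3 = 83%.

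**When a fully adherent patient is lost.** d / (d + L) < 0.5 means L > d. With the day-14 cap, d ≥ 7 gives at least 7/14 = 50%, so a patient with 7 or more allocated days cannot be lost this way. At L = 2 nobody fully adherent is lost: d = 2 gives 2/4 = 50%, which still meets the rule. The rule bites on partly adherent patients. These are plausible, since the pilot cited in the background {6a} reached 4 mL/kg in 65% of patients.

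**Arms compared.** Every day at 6–8 mL/kg fails the ≤ 4.2 rule. In the control arm, the part of that range from 6.0 to 6.6 still passes and anything above 6.6 fails. The burden is therefore mainly, but not only, on ULTV.

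**A case that does not turn on the 48 h reading.** If a patient passes the trial, moves to 6–8 mL/kg, and has deep sedation resumed before 48 h, the interval lies inside the window on either reading. Table 1 includes a step to pressure support at 6–8 mL/kg before deep sedation is resumed.

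**The case against.** The {20c} wording can naturally be read as the onset of a sustained state. {11d} ties the VT change and the lighter sedation target to the same event, so on that reading the gap may be under a day. The second route in {20c}, sedatives stopped, also closes the window for a patient who wakes slowly. The 50% threshold absorbs short lags, and the main analyses are by intention to treat. The full protocol and the case report form are not shown and may settle how days are counted.

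Most of this stands and limits the size. It does not remove the mismatch: the article itself fixes the definition, the thresholds and the window, and failed weaning attempts fall inside the window on either reading.

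A reader might infer that fully adherent ULTV patients who improve early are excluded outright. For example, 3 allocated days and a 4-day lag give 3/7 = 43% and a contrast of 2.0 × 3/7 = 0.86 mL/kg. The documents do not support this as a typical case. Four days at RASS −3 or deeper with sedatives running after a passed trial conflicts with the {11d} target, and if deep sedation is resumed, {11a} reapplies the allocated VT. The result also turns on when VT is charted: if day 4 is recorded before that day's trial, the share is 4/7 = 57% and the patient stays in.

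Nor is a window-average VT a planned statistic. The Secondary outcomes section lists daily values. Days 1 and 2, before any weaning trial, are unaffected.

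**Conclusion.** The mismatch is real and lies in the text. Protocol-mandated days at 6–8 mL/kg can fall inside the adherence window and, by the same wording, the respiratory window. They count against ULTV by design and against control only above 6.6 mL/kg, and they narrow the VT contrast on those days.

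The size rests on an unknown lag. It is nil at zero lag. With an assumed 2-day lag, the contrast over a patient's window drops from 2.0 to between 1.2 and 1.7 mL/kg for 3 to 12 allocated days, and the adherence bar on allocated days rises from 50% to between 58% and 83%. Exclusion of a fully adherent patient needs more lag days than allocated days. The direction assumes patients managed to protocol: someone lightly sedated before passing the trial, a deviation, could leave the window before the allocated VT ends.

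Only the secondary per-protocol analysis and the daily respiratory comparisons are touched. The point is worth correcting but does not threaten the primary result.

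**What to change.** Reconcile {11a}, {11d}, the Secondary outcomes section and {20c} on the analysis side; no clinical rule needs to change. Compute per-protocol adherence and the daily respiratory comparisons only over days on which the allocated strategy applies: from inclusion to weaning-trial success or day 14, plus any period up to day 14 in which deep sedation and the allocated strategy are resumed. If the RASS-based window is kept for description, state that the 48 h counts from its onset.

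The cost is small: revised wording in two places. The dates of weaning-trial success and of any resumption must be available. Adherence is already recorded daily for the first 14 days ({11c}), but the sponsor should confirm that the electronic case report form holds those dates.

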6.Value of daily sedation dose (midazolam, propofol, and opioid) during the first 14 days after inclusion.Opioid doses will be expressed as morphine equivalent (1 mg fentanyl = 100 mg morphine, 1 mg sufentanil = 1000 mg morphine).7.The use of rescue therapy (i.e., muscle relaxant, prone position, inhaled nitric oxide, recruiting maneuvers, ECMO) during the first 14 days after inclusion.8.Severe mixed acidosis, ventilator-associated pneumonia, acute cor pulmonale, barotrauma, and any serious adverse events during the first 28 days after inclusion.Severe mixed acidosis will be defined as the association of pH < 7.15 and PaCO_2_ > 45 mmHg.Ventilator-associated pneumonia will be reported as clinically diagnosed by the attending physician.Acute cor pulmonale will be defined as the association of right ventricle dilatation (right ventricle surface/left ventricle surface > 0.6) and septal dyskinesia assessed by echocardiography.Barotrauma will be defined as the occurrence of any pneumothorax, pneumomediastinum, subcutaneous emphysema, or pneumatocele of more than 2 cm.Serious adverse event will be defined as any adverse event resulting in death, leading to a life-threatening condition, resulting in hospitalization or prolongation of hospitalization, resulting in disability or permanent damage, and resulting any other important medical event.9.Montreal Cognitive Assessment (T-MoCA) test [15] assessed by a phone call at day 365 after inclusion.10.SF-36 score [16] assessed by a phone call at day 365 after inclusion.11.IES-R score [17] assessed by a phone call at day 365 after inclusion.12.Incremental cost-effectiveness ratios of the innovative strategy compared to the reference strategy at day 90 after inclusion.

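### The day-365 T-MoCA, SF-36 and IES-R comparisons are labelled intention to treat, but as written they compare only survivors who can answer, and can be biased in either direction

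*Protocol article*

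**What the plan says.** All references are to the protocol article.

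- **Objectives {7}** lists cognition, quality of life and post-traumatic stress at day 365 as effects of ULTV to be tested.
- **Secondary outcomes**, items 9 to 11, obtains all three by telephone, for example "SF-36 score [16] assessed by a phone call at day 365 after inclusion".
- **Analysis of the primary outcome** defines intention to treat as every included patient analysed in the randomised group. **Analysis of the secondary outcomes** carries this over: "The analysis of the secondary objectives will also be carried out by intention to treat". Quantitative outcomes are compared by Student's t or the Mann-Whitney test.
- **Section {20c}** states: "No method of imputation will be used to replace missing data".
- **Sample size {14}** assumes "Ninety-day mortality 45% in the control group, and 40% in the intervention group".
- **Primary outcome** does fix how death counts elsewhere. Death is the worst result in the composite, and ventilator-free days (VFD) are 0 for a death by day 60. The article gives no such rule for the three day-365 scores.
- **Section {18b}** expects missing day-90 and day-365 data among patients who survive to hospital discharge. Its fallback through next of kin or the general practitioner restores contact or vital status. It does not supply a score.

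**The concern.** A patient who has died has no T-MoCA, SF-36 or IES-R value. With an all-patients analysis set, a two-sample test and no imputation, the dead drop out of the test and only survivors who can answer remain. Survival is itself an outcome that the trial expects ULTV to change, so randomisation no longer protects the comparison.

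If ULTV saves frailer patients, they enter the ULTV mean and have no counterpart in the control mean. ULTV can then look worse on cognition or quality of life although no patient was made worse. If ULTV raises mortality, the same mechanism can make it look better.

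Dissemination plans {31a} foresees a separate publication on day-365 follow-up. There these comparisons would be central, and the label would invite readers to take them as randomised evidence.

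**Working it through.** **Inputs.** Sample size {14} gives day-90 mortality of 45% and 40%, VFD of "28 ± 16.5 in the control group and 34.5 ± 13 in the intervention group", and 100 patients per arm. The significance level used here is two-sided 0.05, as in that section: "The power was computed as the proportion of tests with a bilateral *p*-value < 0.05". Analysis of the secondary outcomes prints "The comparisons will be considered statistically significant for a bilateral *p*-value < 0.5", which conflicts with it and is a separate point. The documents give no relation between frailty and the day-365 scores, so that is varied below as an assumption.

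**1. The plan's own figure.** The plan says that "the inclusion of 100 patients per group will achieve a power greater than 80"%. Simulating its design (3000 datasets, Mann-Whitney on each patient's cross-arm score) gives 80.8% to 82.6%, depending on how VFD is bounded. The mortality inputs are therefore read as the plan uses them. This does not endorse that test: with identical arms it rejected in 87% of simulations, whereas ranking the composite directly rejected in 4.9%. That is outside this point but matters for the fix.

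**2. Who can be scored.** Control: 100 × (1 − 0.45) = 55. ULTV: 100 × (1 − 0.40) = 60. Unscorable by death: (45 + 40)/200 = 42.5%. This is a minimum, because deaths from day 90 to day 365 and non-response add to it. With 110 per arm the survivors are 60.5 and 66.

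**3. Bias if ULTV only prevents deaths and has no effect on the score.**

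- Share of ULTV survivors without a control counterpart: (0.60 − 0.55)/0.60 = 8.3%, or 5 of 60.
- If these patients score d SD below the other survivors, bias = 0.083 × d.
- Standard error: √(1/55 + 1/60) = 0.187 SD.
- P(significant false harm) = Φ(bias/SE − 1.96), which is 2.5% without bias.

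| Assumed d | Bias (SD) | Bias/SE | Significant false harm | Estimate on the harm side |
|---|---|---|---|---|
| 0.5 | 0.042 | 0.22 | 4.1% | 59% |
| 1 | 0.083 | 0.45 | 6.5% | 67% |
| 2 | 0.167 | 0.89 | 14.3% | 81% |

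An expected z of 1.96 would need d = 1.96 × 0.187/0.083, about 4.4 SD.

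**4. A score fully correlated with survival.** If the lowest-scoring fraction p of a normal score dies, with z the p-quantile, the survivors' mean is λ = φ(z)/(1 − p).

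- λ is 0.720 at p = 0.45 and 0.644 at p = 0.40, a shift of −0.076 SD against ULTV.
- Against the SE above this is 0.076/0.187 = 0.4 SE.
- That ratio takes the survivors' SD as 1. Under this model their variance is 1 + zλ − λ², which is 0.392 and 0.422. The SE is then √(0.392/55 + 0.422/60) = 0.119, and the shift is 0.64 SE, or 0.12 of the survivors' SD. P(significant false harm) = Φ(0.64 − 1.96), about 9%.

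**5. Partial correlation.** A latent-frailty simulation (4000 datasets) with correlations of 0.3 to 0.9 gives a bias of 0.02 to 0.10 survivors' SD and significant false harm in 3.1% to 7.2% of trials.

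**6. Other mortality effects.** With 45% versus 35%, the share is 0.10/0.65 = 0.154. At d = 1 the bias is 0.154 SD and significant false harm occurs in 13.1% of trials. If ULTV instead raised mortality by 5 points, from 45% to 50%, 5/55 = 9.1% of control survivors would have no ULTV counterpart. At d = 1 the bias would be 0.091 SD in favour of ULTV.

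**7. Ranking death worst.** In the step 5 model (correlations 0 to 0.9), an all-randomised Mann-Whitney test gives significant harm in 0.5% to 0.9% of trials and significant benefit in 6% to 10%, with no effect on the score. The result mostly reflects mortality.

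**The case against.** - **The no-imputation rule is not the error.** This stands. Inventing scores for the dead would be wrong, and the rule does not forbid ranking death. The fault lies in the analysis set and its label.
- **A rule for death may be in the full protocol or analysis plan.** Possibly. But the article itself fixes the analysis set, the tests and the missing-data rule, and the point concerns what those produce together.
- **A reader might infer that the trial is likely to report false harm from ULTV.** The documents do not support this. One can draw an alarming picture: 30% impairment among control survivors (16.5/55) and impairment in all 5 extra ULTV survivors gives 21.5/60 = 35.8%, an apparent harm of 5.8 points. Neither assumption is in the article, which gives no T-MoCA cut-off. The standard error, √(0.30 × 0.70/55 + 0.358 × 0.642/60), is 8.7 points, so this is about 0.7 SE. The direction is also assumed. Survivors too impaired for a telephone test drop out as well, which would partly offset a bias against ULTV.
- **Ranking death worst answers a different question.** This stands too. Such a test largely repeats the mortality comparison and can hide real impairment, so it should not be the only between-arm comparison.
- **Readers will see the denominators.** Partly. Mortality and the frequency of missing data are to be described by arm, but the article does not separate death from loss to follow-up for these scores.

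**Conclusion.** The point holds for three secondary outcomes. Followed as written, the day-365 comparisons are restricted to survivors who can answer, so the intention-to-treat label contradicts the article's own definition. This does not depend on the size of any bias.

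The bias can go either way. At the planned 5-point mortality difference it is modest: about 0.08 SD and 0.4 SE for a fully correlated score, or 0.6 SE once the survivors' narrower spread is counted. A significant false harm is unlikely, at about 3% to 7% in the frailty simulations against 2.5% with no bias. A larger mortality effect, or extra survivors with a much larger deficit, would increase it. These figures rest on the plan's assumed day-90 mortality and on assumed links between frailty and score. The primary conclusion is unaffected.

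**What to change.** For items 9 to 11:

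1. Replace the intention-to-treat label with 'among day-365 survivors who completed the assessment'.
2. Separate death by day 365, loss to follow-up and inability to answer, and report each by arm beside the scores.
3. Add a supportive Mann-Whitney analysis of T-MoCA and SF-36 in all randomised patients, with death by day 365 ranked worst, the ordering the composite already uses. Rank patients directly in one pooled ordering. Do not apply the test to cross-arm scores, given the 87% rejection under the null in step 1. IES-R is left out because a comparable analysis by positive screen would need a cut-off that the article does not give.
4. Interpret a survivors-only difference, in either direction, only together with that analysis.

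The cost is analysis wording and one case-report-form field for why the interview was not done. Assessors are unblinded, so the categories for that field should be defined in advance. The ranked analysis mixes mortality with function, so it supplements the survivors-only comparison and does not replace it.
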